### Background and rationale

1.1

Head and neck cancer arises from the epithelial lining of the upper aerodigestive tract and represents the seventh most common malignancy worldwide (1). Radiotherapy, either alone or in combination with concurrent chemotherapy, remains a cornerstone in the management of these malignancies (2). However, these treatment strategies are commonly associated with wide range of oral complications, including oral mucositis, secondary infections, xerostomia, dysgeusia, pain and an increased risk of dental and periodontal diseases. These complications impair essential activities like eating, swallowing, speaking and thereby reducing quality of life of patients. In severe cases, they may lead to treatment interruptions, infections and compromised oncological outcomes (3, 4).

Among the complications, oral mucositis (OM) is one of the most dose limiting toxicity of cancer treatment and it is featured by inflammation and ulceration of oral mucosa, typically developing 5–7 days after the initiation of chemo and radiotherapy. Approximately 40% of head and neck cancer patients receiving chemotherapy alone develop OM, whereas 90%–100% patients receiving concurrent chemo-radiotherapy (5). Evidence from Indian clinical settings indicated that radiation-induced oral mucositis (RIOM) usually appears after a cumulative radiation dose of approximately 20Gy, becomes more widespread at around 30Gy, and reaches peak severity with Grade 3 reactions at cumulative doses of 66 – 70Gy (6).

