#### Inclusion criteria

2.3.1

Participants aged 20–75 years of any gender, diagnosed with head and neck cancers involving the oral cavity and/or oropharynx and scheduled to undergo radiotherapy for a period of 4–7 weeks with a total radiation dose of 55–72 Gy, will be eligible for inclusion in the study. Only those who are willing to participate and are willing to provide written informed consent before the enrolment, will be included.

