#### Intervention description

2.4.1

Arm A will constitute the intervention group, in which participants will receive the Siddha regimen as an adjunct to SOC during the entire course of radiotherapy and the post-radiotherapy period. Participants will be assessed weekly throughout the study duration or until complete recovery from oral mucositis, whichever occurs earlier.

***Procurement of trial drugs:*** The interventional drugs will be procured from GMP certified manufacturers. TPC will be procured from TAMPCOL, Chennai and GV will be procured from IMPCOPS, Chennai.

***Method of drug administration:*** The Siddha intervention will consist of TPC mouthwash and topical application of GV, administered as follows. TPC mouthwash will be prepared using pre-measured teabags, each containing 2 g of TPC. Participants will be instructed to immerse one teabag in 60 mL of freshly boiled water and allow it to stay immersed for 10–15 min, until the solution cools to room temperature. The teabag will then be removed, and the resulting solution will be used immediately as a mouth rinse. Fresh preparation will be performed prior to each use. Then, participants will be instructed to rinse with 60 mL of the mouthwash at each time point, three times daily after meals, swishing for 30seconds and then spitting out the solution. The mouthwash regimen will commence on day0 (one day prior to initiation of radiotherapy) and will continue during radiation therapy and 6weeks post radiation therapy. In addition, GV will be administered at a dose of 10 g per day, applied topically within the oral cavity three times daily, following mouth rinsing. Depending on the clinical schedule, treatment may be initiated on the same day as radiotherapy in some participants.

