### Outcomes

2.5

The primary outcome of the study is the severity of RIOM, assessed using RTOG grading scale. This will be measured as the proportion of participants who develop severe oral mucositis (RTOG grade ≥ 3) at any time during radiotherapy and up to six weeks following completion of radiotherapy, compared between the two study arms. The primary outcome will be assessed from randomisation until the last day of study medication use.

The secondary outcomes include oral mucositis severity assessed using WHO oral mucositis scale, measured as the proportionate reduction in the occurrence and severity of mucositis during radiotherapy and up to six weeks post-radiotherapy. Oral cavity pain, evaluated using VAS as the proportion of participants achieving a minimum two-point reduction in pain intensity and analgesic usage, assessed as the percentage of participants requiring analgesics categorised according to WHO three-step analgesic ladder. Safety outcomes will be evaluated by documenting the number of adverse events reported in each study group. Treatment interruption will be assessed as the proportion of participants experiencing one or more radiotherapy interruptions due to severe RIOM and the total number of days of missed radiotherapy. In addition, body weight changes during radiotherapy, requirement for nasogastric tube feeding, and interruptions in oral intake will be documented as exploratory indicators of nutritional impact. All secondary outcomes, except treatment interruption, will be assessed from randomisation until the last day of study medication use, while treatment interruption will be evaluated until the completion of radiotherapy.

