### Participant timeline

2.6

Participants will undergo initial screening and randomisation at baseline, followed by a 14-week observation period comprising weekly clinical evaluations and periodic laboratory assessments as detailed in the timeline below (Table 2).

**Table 2 T2:** Schedule of enrolment, interventions, and assessments.

Activity/Assessment	Baseline	W1	W2	W3	W4	W5	W6	W7	W8	W9	W10	W11	W12	W13
Enrolment														
Screening & Informed Consent	X													
Randomisation & Allocation	X													
Intervention														
Study Intervention	X	X	X	X	X	X	X	X	X	X	X	X	X	X
Efficacy Assessment														
RTOG Scale	X	X	X	X	X	X	X	X	X					X
WHO oral mucositis Scale	X	X	X	X	X	X	X	X	X	X	X	X	X	X
VAS		X	X	X	X	X	X	X	X	X	X	X	X	X
WHO 3-step analgesic ladder		X	X	X	X	X	X	X	X	X	X	X	X	X
Interruption of RT		X	X	X	X	X	X	X	X					
Days of Missed RT		X	X	X	X	X	X	X	X					
Safety & Laboratory Assessment														
Safety Monitoring		X	X	X	X	X	X	X	X	X	X	X	X	X
CBC	X								X					X
LFT	X								X					X
RFT	X								X					X

RT, radiotherapy; RTOG, Radiation Therapy Oncology Group; WHO, World Health Organization; VAS, visual analogue scale; CBC, complete blood count; LFT, liver function test; RFT, renal function Test; W1−13, No. of week.

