### Plans for assessment and data collection

4.1

Potential participants will be screened by trained investigators to ensure compliance with the inclusion and exclusion criteria. Screening will include a review of medical records and current radiotherapy or chemoradiotherapy details to confirm the diagnosis of head and neck cancer. Eligible participants will be informed about the study objectives, procedures, risks, and benefits, and written informed consent will be obtained prior to enrolment. All screening details will be documented in the screening form and case record form (CRF), with reasons recorded for screen failures. Participants meeting eligibility criteria will proceed to baseline assessments, randomisation, and initiation of the allocated intervention.

At the screening or baseline visit, detailed clinical and drug histories will be recorded. Clinical examination will then be performed to assess the oral mucositis severity using the RTOG and WHO Oral Mucositis Scales during baseline visit. Baseline laboratory investigations, including complete blood count (CBC), liver function test (LFT), and renal function test (RFT), will be performed. Participants will then be randomised, and study medications will be dispensed as per group allocation. Follow-up assessments will be conducted weekly by trained assessors throughout the course of radiotherapy, with telephonic follow-up continued up to six weeks post-radiotherapy. The severity of oral mucositis will be assessed using RTOG and WHO oral mucositis scales, pain intensity will be measured using a 10-point VAS, and analgesic use will be documented according to WHO three-step analgesic ladder. Details of the grading criteria for all these four scales are presented in Table 3. However, in certain clinical situations, analgesics, particularly opioids, may be prescribed for cancer-related pain rather than for RIOM. In such cases, the indication for analgesic use may not directly reflect RIOM severity. To address this, all analgesic usage will be documented along with the primary indication, and cases where analgesics are administered for non-RIOM-related pain, will be clearly specified with appropriate justification. All assessors and physicians involved in outcome evaluation will be trained in advance regarding grading scales and assessment procedures.

**Table 3 T3:** Assessment scales used for outcome evaluation.

Assessment Tool	Grade/Scale	Grading Description

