### Statistical methods

4.5

Baseline demographic and clinical characteristics of the participants will be summarised using descriptive statistical methods. Categorical data will be presented as frequencies and percentages, whereas continuous data will be expressed either as mean ± standard deviation or as median with interquartile range, based on the distribution of the data.

The primary outcome of the study, namely the severity of oral mucositis assessed using RTOG and WHO oral mucositis scales, will be analysed by comparing the proportion of participants who develop grade ≥2 mucositis in the two study groups. Depending on the suitability of the data, either the chi-square test or Fisher's exact test will be used for comparison. In addition, weekly mucositis grade distributions will be analysed to observe changes in severity, recovery patterns, and overall trends during treatment and follow-up.

For secondary outcomes, pain intensity measured using VAS will be compared between the groups at each assessment point using either the independent samples t-test or the Mann–Whitney U test, based on the data distribution. Analgesic use, categorised according to WHO three-step analgesic ladder, will be analysed as categorical data and compared between groups using the chi-square test or Fisher's exact test. Rescue medication use will be analyzed as a secondary outcome to compare overall analgesic requirements between the study groups. Laboratory investigations will be summarised descriptively and assessed for safety through appropriate within-group and between-group analyses.

The distribution of continuous variables will be checked using histograms to determine normality. Depending on the nature of the data, either parametric or non-parametric statistical methods will be applied for between-group comparisons. Subgroup analyses based on cancer treatment modalities will also be carried out to explore whether the treatment effects remain consistent across clinically relevant subgroups. However, these analyses will be considered exploratory in nature.

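### The two-point VAS reduction has no stated reference time and no baseline VAS behind it, can count prevented pain as failure, and is not the quantity that section 4.5 analyses

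*Protocol article*

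**What the plan says.** **Outcome.** Section 2.5 has oral cavity pain "evaluated using VAS as the proportion of participants achieving a minimum two-point reduction in pain intensity". No reference time is given. The same section sets the window: "All secondary outcomes, except treatment interruption, will be assessed from randomisation until the last day of study medication use".

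**Schedule.** Table 2 (section 2.6) has 14 visit columns, Baseline and W1 to W13. The VAS row reads "VAS X X X X X X X X X X X X X": 13 marks, with the baseline cell empty. The WHO mucositis row has 14 marks, including baseline. Section 4.1 agrees with the table: "Clinical examination will then be performed to assess the oral mucositis severity using the RTOG and WHO Oral Mucositis Scales during baseline visit". VAS is not named at that visit.

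**Population and start.** Section 2.3.1 enrols people "scheduled to undergo radiotherapy for a period of 4–7 weeks with a total radiation dose of 55–72 Gy"; neither mucositis nor pain is required. Section 2.4.1 adds: "The mouthwash regimen will commence on day0 (one day prior to initiation of radiotherapy", or on the same day in some participants. Section 1.1 describes mucositis as "typically developing 5–7 days after the initiation of chemo and radiotherapy".

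**Objective and analysis.** Section 1.3 aims to compare pain intensity between groups week by week. Section 4.5 says "pain intensity measured using VAS will be compared between the groups at each assessment point using either the independent samples t-test" or a Mann–Whitney test. It plans no comparison of responder proportions for pain.

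**The concern.** A reduction needs a starting value. This regimen begins before the injury, and pain is expected to rise and then recede. An outcome that rewards a fall in pain suits patients who are already in pain. Here it can reward only those who first develop pain, so a participant in whom pain is prevented cannot succeed.

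Two things are at stake. First, the pain outcome as defined could favour the arm with more pain, and the choice of reference is left open until data exist. Second, the objective, the outcome and the analysis describe different quantities, so the trial has no single stated answer on pain.

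**Working it through.** The article gives no sample size, power or expected rate for pain, so there is no figure of the plan's own to reproduce. The check takes each possible reference in turn.

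**Constraint.** VAS runs from 0 to 10 (Table 3). A fall of at least 2 points to a score of 0 or more needs a reference score of at least 2.

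**(a) Baseline reference.** No value is collected, so the change cannot be computed. Had it been collected and been 0 or 1, response would be impossible in either arm.

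**(b) W1 reference.** This can be computed, but W1 comes after treatment has started. Section 1.1 gives onset at 5–7 days, which is about W1. It also says that mucositis usually appears after about 20 Gy. At the extremes of section 2.3.1 the weekly dose is 72/4 = 18 Gy or 55/7 = 7.9 Gy, so 20 Gy is reached after 20/18 = 1.1 to 20/7.9 = 2.5 weeks. On either statement, W1 lies at or before onset and most later pain would be a rise from it.

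**(c) Own-peak reference.** This can also be computed. A participant whose VAS never exceeds 1 is always a non-responder; one who goes from 8 to 6 is a responder.

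**Illustration of direction.** A simulation used 13 weekly scores rising from about 0 at W1 to a peak at W7 and falling close to 0 by W13. The individual peaks had an SD of 2. The curve, the SD and the mean peaks are assumptions, and the recovery pattern is the same in every row.

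| Assumed mean peak VAS | Responders, own peak to W13 | Responders, W1 to any later week |
|---|---|---|
| 7 | 99.7% | 0.1% |
| 5 | 96% | 0.1% |
| 3 | 80% | 0.1% |
| 1.5 | 56% | 0.1% |

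With the peak as reference, less pain gives a lower success rate. With W1 as reference, almost nobody responds, whatever happens later.

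**Sections side by side.** Section 1.3 concerns weekly pain intensity. Section 2.5 concerns a proportion of responders. Section 4.5 tests weekly scores. Sections 1.3 and 4.5 agree with each other; section 2.5 agrees with neither, and a t-test or Mann–Whitney test on scores does not compare the proportion it defines.

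**Side point: weekly tests.** Section 4.5 counts a two-sided p of 0.05 or less as significant. With 13 independent tests the chance of at least one false positive is 1 − 0.95^13 = 48.7%. Simulation with first-order autocorrelation gives about 36% at 0.7, 31% at 0.8 and 23% at 0.9. The correlations are assumptions; the document gives none.

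**The case against.** The strongest reply is that the outcome is under-specified and no worse than that. VAS is recorded at W1 to W13, so a reduction from W1 or from the peak can be calculated. A reader might infer that the outcome cannot be computed at all; the document supports this only for change from baseline. That limit stands. It does not rescue the outcome, because section 2.5 names neither alternative and both suit a preventive regimen badly.

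A reader might also put a large number on the inversion. If 40% of Arm A and 10% of Arm B never reached a VAS of 2, and everyone else later fell by two points, success would be 60% against 90%. Nothing in the article supports those rates. Section 1.1 puts mucositis at 90–100% under concurrent chemoradiotherapy, so the pain-free group may be small. The example also leaves out any faster recovery in Arm A, which would push the result the other way. Only the direction of the risk is established.

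The weekly tests concern a secondary outcome of a phase II trial and match the objective in section 1.3. Choosing a summary measure or a multiplicity adjustment is commonly left to an analysis plan. That is fair, and it is why multiplicity is only a side point. An analysis plan cannot, however, supply a baseline score that was never taken.

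Section 2.2 describes participants as already having mucositis, which may explain why a reduction was chosen. It conflicts with sections 2.3.1 and 2.4.1, and it provides no baseline VAS.

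**Conclusion.** The point holds as a defect in the definition of one secondary outcome. The two-point reduction has no reference time; change from baseline cannot be computed; the two references that can be computed are unnamed and unsuitable; and section 4.5 does not analyse the proportion. With an own-peak reference, a participant whose VAS stays below 2 always counts as a failure. This follows from the scale alone and needs no assumption. How far it would distort the comparison between arms cannot be derived from the document.

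The uncorrected weekly tests add a chance of roughly 23% to 49% of at least one false positive, for 13 tests and an assumed autocorrelation between 0.9 and 0.

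It would be wrong to infer that the pain data are lost or that the primary outcome is affected. The weekly scores remain usable for the objective in section 1.3. The matter is pressing because enrolment has begun, and every further participant enrolled without a baseline VAS loses it for good.

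**What to change.** 1. Add VAS to the baseline column of Table 2 and to the baseline visit in section 4.1, for participants still to be enrolled.
2. Replace the two-point reduction with one summary of the weekly scores, compared once between arms. Mean weekly VAS (area under the curve) from W1 to six weeks after radiotherapy is a suitable choice. Report weekly values, peak VAS and the proportion with VAS of 7 or more (Table 3's severe band) as supportive.
3. Deal with weeks after recovery. Sections 2.4.1 and 2.4.2 end assessments at recovery if that comes first, so a mean over observed weeks would drop the low scores of early recoverers and again work against the better arm. Either continue VAS by telephone, using the weekly calls already planned in section 6.5, or state a rule, for example carrying the recovery score forward with a sensitivity analysis.
4. Adjust for baseline VAS where it was collected. For those already enrolled, use a missing-indicator or an unadjusted comparison, which randomisation keeps valid. Do not set their baseline to 0: sections 2.2 and 4.1 allow for post-operative patients and cancer-related pain.
5. Align sections 1.3, 2.5, 2.6 and 4.5, and do so before the interim analyses in section 5.1 bring outcome data into view.

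The cost is one extra self-rated score at an existing visit and revised wording, plus VAS by telephone after recovery if that option is taken. The downside is that baseline adjustment is not available for participants already enrolled.

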### Objectives

1.3

The primary objective of this study is to evaluate the proportionate reduction in the occurrence of severe RIOM, as assessed using RTOG grading scale, among participants receiving a Siddha regimen as an adjunct to standard care compared with those receiving standard care alone, assessed during radiotherapy and at six weeks post-radiotherapy.

The secondary objectives are to assess the proportionate reduction in the severity of radiation-induced oral mucositis using WHO oral mucositis scale at the same time points; to compare oral cavity pain intensity between the study groups using VAS, assessed weekly throughout the study period; to evaluate changes in analgesic usage, including escalation or de-escalation according to the WHO Three-Step Analgesic Ladder, on a weekly basis during the study period; to estimate and compare the proportion of adverse reactions between the study groups; and to evaluate differences in the frequency and duration of treatment interruptions attributable to oral mucositis between the study groups.

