### Adverse event reporting and harms

5.2

Any adverse event occurring after the signing of the informed consent but prior to initiation of the study intervention will be recorded and reported as not related to the study drug. All adverse events occurring from study enrolment until trial completion will be documented and graded using the National Cancer Institute Common Terminology Criteria for Adverse Events (CTCAE), Version 5.0. Any adverse event meeting the criteria for a serious adverse event (SAE) during this period will be reported to the institutional ethics committee (IEC) in accordance with applicable guidelines. Serious adverse events occurring after participant discontinuation will not be reported unless, in the opinion of the investigator, the event is considered possibly related to the study intervention or a study-related procedure. The relationship of adverse events to the study drug will be assessed by the investigators based on temporal association with drug administration and whether the event is unexpected or unexplained in the context of the participant's clinical course, pre-existing medical conditions, and concomitant medications. TPC, when used as an internal medicine, has been associated with suspected adverse drug reactions such as nausea, vomiting, and loose stools, as reported in pharmacovigilance databases. However, no adverse drug reaction reports have been identified for its use as a mouthwash. Based on its safety profile with internal administration, the expected adverse effects in this study may include mild gastrointestinal symptoms such as nausea and vomiting.

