#### Interventions - modifications

5.2.1

Participants who develop adverse reactions that are considered intolerable to the Siddha medicines will have the study intervention discontinued, and the event will be recorded as an adverse reaction. In rare instances of suspected allergic reactions, including skin manifestations, the trial medication will be immediately withdrawn, and the event will be documented as an adverse event. If any biochemical abnormalities are detected during routine laboratory investigations, the study medication will be temporarily withheld until the laboratory values return to normal or clinically acceptable limits. Once the parameters stabilise, the intervention may be restarted at half of the earlier dose, based on the investigator's clinical judgment. In cases where the biochemical abnormalities reappear, the study medication will be permanently discontinued and documented as an adverse event. Even if the assigned intervention is modified or stopped, participants will be encouraged to continue follow-up with the study team so that outcome assessments and relevant study data can still be collected, thereby reducing the possibility of missing data.

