## Conclusion

8

In conclusion, this study is an effort to scientifically evaluate the role of Siddha medicine as an adjunct to contemporary oncology care in the management of RIOM. The study aims to address an important supportive-care need through the use of accessible, affordable, and culturally acceptable interventions. If Siddha regimen is found to be more effective than SOC alone in reducing severe RIOM, pain, and treatment interruptions without causing additional toxicity, it may contribute to improving patient-centred care in head and neck cancer radiotherapy settings. The findings may also help support the development of integrative oncology practices and future national guidelines.

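### Safety objective, outcome, window and analysis population do not agree, so the between-arm comparison of harm is not fixed, although the planned data could support one

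*Protocol article*

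**What the plan says.** All references are to the protocol article.

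- **1.3 Objectives:** one secondary objective is "to estimate and compare the proportion of adverse reactions between the study groups".
- **2.5 Outcomes:** "Safety outcomes will be evaluated by documenting the number of adverse events reported in each study group". Every secondary outcome except treatment interruption runs from randomisation to the last day on which study medication is used.
- **5.2 Adverse event reporting and harms:** every adverse event from enrolment to the end of the trial is documented and graded by CTCAE version 5.0, with no restriction by arm or relatedness. On causality, "The relationship of adverse events to the study drug will be assessed by the investigators based on temporal association with drug administration" and on whether the event is otherwise unexplained. On late serious events, "Serious adverse events occurring after participant discontinuation will not be reported unless, in the opinion of the investigator", it is thought possibly related to the intervention or a study procedure.
- **5.2.1 Interventions - modifications:** "Participants who develop adverse reactions that are considered intolerable to the Siddha medicines will have the study intervention discontinued". Participants whose intervention is changed or stopped are encouraged to stay in follow-up.
- **4.5 Statistical methods:** safety is analysed in the per-protocol population. Laboratory values are compared within and between groups.
- **8 Conclusion:** the hoped-for result is benefit "without causing additional toxicity".

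**The concern.** The trial sets out to compare harm between arms, and its closing section makes toxicity one of the conditions for supporting the regimen. The objective and the outcome describe different quantities. The objective depends on a causality judgement that may be possible in only one arm. The outcome window may close at the moment a participant stops treatment because of harm, and the analysis population may leave that participant out.

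These faults do not all pull the same way. A reaction comparison tied to the Siddha medicines is loaded against Arm A. A window that ends at the last dose, together with a per-protocol population, can hide excess harm in Arm A. A team that follows the article literally could therefore report either answer, depending on which sentence it uses.

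**Working it through.** The article gives no adverse event rate, safety margin or safety power, so there is no figure to reproduce. The check compares the sections and then uses small illustrations. Those use 80 per arm (section 2.7: 64/(1 − 0.20) = 80), or 64 after the allowed dropout. All event rates below are assumptions.

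**1. Event and unit.** Section 1.3 has reactions as a proportion, without stating a denominator. Section 2.5 has all events as a count. Suppose each arm has 20 events. In Arm A they fall on 20 participants, 20/80 = 25%. In Arm B they could fall on anything from 20 participants (25%) to 5 participants with four events each (5/80 = 6.25%). The counts are equal throughout. At the extreme, Fisher's exact test on participants gives p = 0.0018. The two metrics can therefore disagree.

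**2. Causality.** The article does not define *study drug*. Several places suggest the Siddha regimen: the procurement text in 2.4.1 covers only the two Siddha preparations, 5.2 gives expected effects only for one of them, and 5.2.1 ties intolerable reactions to the Siddha medicines. Against that, 4.1 says "study medications will be dispensed as per group allocation", and Table 1 lists benzydamine beside the Siddha drugs. If the narrow reading is meant, Arm B has zero reactions by definition. With k reactions in Arm A and none in Arm B, the two-sided Fisher p is 2 × C(80,k)/C(160,k):

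- k = 5 (6.25%): p = 0.059
- k = 6 (7.5%): p = 0.028
- k = 8 (10%): p = 0.0065

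With 64 per arm, six reactions (9.4%) also give p = 0.028. These p-values say nothing about excess harm, because the same symptoms in Arm B could not be counted as reactions. An all-cause comparison does not have this problem.

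**3. Window.** Section 2.5 stops at the last day of study medication, and 5.2 runs to the end of the trial. For participants who complete treatment the two largely coincide, since treatment continues for six weeks after radiotherapy (2.4.1, 6.5). They part for participants who stop early. Section 5.2.1 stops the intervention for intolerance to the Siddha medicines, which only Arm A receives, and still encourages follow-up. Taken literally, 2.5 discards events recorded in that follow-up.

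**4. Population.** Section 2.3.3 allows withdrawal for serious or intolerable reactions and for compliance below 70%. A per-protocol safety set (4.5) may then exclude the participants most likely to have been harmed.

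**5. What an all-cause comparison could detect.** For the proportion with at least one event of a given type, two-sided 0.05:

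power = Φ{ [|p₁ − p₂| − 1.96·√(2p̄(1 − p̄)/n)] / √([p₁(1 − p₁) + p₂(1 − p₂)]/n) }

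| Assumed rates | n = 64 | n = 80 |
|---|---|---|
| 5% vs 10% | 19% | 22% |
| 10% vs 20% | 35% | 42% |
| 10% vs 25% | 61% | 71% |
| 10% vs 30% | 82% | 89% |

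A large excess is detectable, but a modest one mostly is not.

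**The case against.** The strongest reply is that the trial already collects what is needed. Allocation is randomised 1:1 against standard care alone, all adverse events are documented and graded in both arms, safety monitoring is weekly from week 1 to week 13, and laboratory values are compared between groups. Causality plays no part in the outcome as 2.5 words it. This stands. A reader might infer that the trial cannot show whether the regimen adds toxicity, or offers no randomised comparison of harm. The documents do not support either inference.

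Four further limits also stand:

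- The zero in Arm B depends on how an undefined term is read. The Discussion itself says that standard care can cause burning and altered taste, so Arm B could have reactions under a wider definition.
- The late-SAE sentence follows one about reporting to the ethics committee. It may restrict only that reporting, and *discontinuation* there may mean leaving the study. Loss of SAE data is possible but not shown.
- Treatment lasts 10 to 13 weeks according to radiation dose. That is not a difference between arms.
- Detailed safety tables are normally left to the full protocol or SAP, and the Conclusion's sentence is conditional.

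These points do not remove the conflict. The objective, outcome, window and population are all stated in this article, and they do not agree.

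**Conclusion.** The point holds in a limited form. The stated safety objective and outcome differ in event and unit, the window is given in two ways that part for participants who stop early, and the per-protocol safety set compounds this. The data to be collected can support a valid all-cause comparison, but the text does not specify one.

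The size of any resulting bias cannot be computed, because the article gives no event rates. The illustrations rest on assumed counts, and the one-sided reaction comparison rests on reading *study drug* as the Siddha medicines only. The correction should be made, because a conclusion on toxicity could otherwise turn on which sentence is followed. It does not undermine the trial's design.

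**What to change.** 1. In 1.3, 2.5 and 5.2, state one between-arm safety outcome: the proportion of participants with at least one adverse event of any cause, and likewise with any event of grade 3 or higher and with any SAE. Give event counts as a supplement.
2. Fix the window from randomisation to six weeks after radiotherapy, whether or not study medication continues.
3. Define *study drug* and *adverse reaction*. Report investigator-judged reactions to the Siddha medicines descriptively for Arm A only, without a between-arm test.
4. Reconcile the late-SAE sentence in 5.2 with the rest of 5.2 and with 5.2.1, so that all SAEs are recorded for the comparison, whatever is reported to the ethics committee.
5. In 4.5, replace the per-protocol safety population with all randomised participants who received study treatment, counting standard care as study treatment in Arm B. Without this change, items 1 and 2 would contradict 4.5.

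The cost is wording in four sections and a few more SAE records. CTCAE grading and follow-up after stopping are already planned. Enrolment has begun, so an early amendment, with a check that events in participants already enrolled have been captured, avoids uneven data. Power for modest excesses stays low, so the results should be given as differences with confidence intervals, and a non-significant difference should not be read as absence of added toxicity.
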